## Abstract

**Background:**

Approximately 8–15% of patients undergoing bariatric surgery develop symptomatic gallstone disease within 24 months after surgery. Ursodeoxycholic acid (UDCA) seems to effectively prevent the formation of gallstones detectable by ultrasound after bariatric surgery. The aim of the UPGRADE trial is to provide evidence on the prophylactic use of UDCA in preventing symptomatic gallstone disease postoperatively.

**Methods:**

The UPGRADE trial is designed as a randomised, placebo-controlled, double-blind multicentre trial in patients with morbid obesity undergoing Roux-en-Y gastric bypass (RYGB) or sleeve gastrectomy (SG). Patients are randomly assigned to either UDCA 900 mg daily for 6 months or placebo treatment. This paper details the statistical analysis plan (SAP) of this trial and was submitted before outcome data were available.

**Results:**

The primary endpoint of this trial is symptomatic gallstone disease within 24 months after bariatric surgery, defined as admission or hospital visit for symptomatic gallstone disease. Secondary outcomes consist of the development of gallstones/sludge on ultrasound at 24 months in the gallstone-negative group at baseline, presence of gallstones/sludge on ultrasound at 24 months, number of cholecystectomies, side effects of UDCA, therapy compliance, quality of life, costs and revenues. Analyses will be completed according to this pre-specified SAP. The main analysis will be performed as a standard ITT analysis using the chi-squared test.

**Discussion:**

The UPGRADE trial will show if prophylactic use of UDCA reduces the incidence of symptomatic gallstone disease after bariatric surgery. Unforeseen deviations from the SAP at the time of analysis will be motivated and discussed.

**Trial registration:**

The Netherlands Trial Register NL5954. Registered on 21 November 2016.

## Introduction

The number of bariatric interventions for morbid obesity is increasing worldwide. Rapid weight loss is a major risk factor for gallstone development. Approximately 8–15% of patients undergoing bariatric surgery develop symptomatic gallstone disease within 2 years after surgery. Prophylactic administration of ursodeoxycholic acid (UDCA), an oral bile acid, can prevent the formation of gallstones after bariatric surgery by reducing bile lithogenicity [1–3]. However, little evidence is available regarding the efficacy of UDCA in preventing symptomatic gallstone disease. The UPGRADE trial (Ursodeoxycholic acid for the prevention of symptomatic gallstone disease after Roux-en-Y gastric bypass and sleeve gastrectomy) is designed to investigate whether UDCA reduces symptomatic gallstone disease after bariatric surgery. The trial protocol was previously published [4], and the present paper is the proposed statistical analysis plan (SAP). This SAP is in line with the corresponding reporting guideline for SAPs [5] and was written without knowledge of the outcomes by the investigators.

## Summary study protocol

The UPGRADE trial is a randomised, placebo-controlled, double-blind multicentre trial comparing the prophylactic use of UDCA versus placebo in patients with morbid obesity undergoing bariatric surgery. Patients with an intact gallbladder and scheduled to undergo Roux-en-Y gastric bypass (RYGB) or sleeve gastrectomy (SG) were included. Patients were excluded in case of the existence of symptomatic gallstone disease prior to bariatric surgery, prior bariatric surgery, prior gallbladder surgery, inflammatory bowel disease and other conditions of the small intestine and liver which may interfere with enterohepatic circulation of bile salts, hypersensitivity to ingredients of UDCA or placebo, and intake of UDCA within the last 30 days before screening. Patients were randomly assigned to either UDCA 900 mg daily for 6 months or placebo in a 1:1 ratio. Randomisation was done prior to surgery with an online computer software program (ALEA AMC, Amsterdam, the Netherlands, version 2.2) and implemented into a web-based application. Randomisation was stratified for the presence of gallstones (yes versus no) and type of surgery (RYGB versus SG) and performed by using random block sizes of 4, 6 and 8. Data are collected during hospitalisation and study visits at 6 weeks (window 4–8 weeks) and 16 weeks (window 14–18 weeks) and at 6 months (window 5–9 months), 12 months (window 10–15 months) and 24 months (window 24–30 months) by standardised case report forms. Questionnaires are gathered at baseline, 6 weeks, and 3, 6, 12, 18 and 24 months (windows 1 week before to 2 weeks after the date of administration). The primary outcome is symptomatic gallstone disease within 24 months, defined as admission or hospital visit for symptomatic gallstone disease. Secondary outcomes consist of the development of gallstones/sludge on ultrasound at 24 months in the gallstone-negative group at baseline (window 18–30 months), presence of gallstones/sludge on ultrasound at 24 months (window 18–30 months), number of cholecystectomies, time to symptomatic gallstone disease and cholecystectomy, side effects of UDCA, therapy compliance, quality of life, costs and revenues. Safety outcomes are adverse events (AEs), serious adverse events (SAEs) and suspected unexpected serious adverse reactions (SUSARs). For the sample size calculation, we refer to the study protocol [4]. On 22 October 2018, all included patients underwent surgery, and complete 2-year follow-up data are expected in November 2020. For the complete study protocol, we refer to the previous publication [4].

### Protocol developments

The UPGRADE is registered at the Netherlands Trial Register (NL5954) on 21 November 2016. The institutional review board (IRB) of the Slotervaart Hospital and Reade, Amsterdam, approved the protocol on 9 November 2016. The trial is conducted in three high-volume bariatric centres. On 18 July 2017, the IRB approved a protocol amendment in which the bariatric procedure SG was added to the inclusion criteria, because of increasing use worldwide, in Europe and in participating centres [6]. The initial study protocol stated that patients had to start the trial medication as soon as possible, but no later than 2 weeks after surgery. We extended the accepted start of trial medication during the initial course of the trial, in case of difficulties taking the trial medication within the first 2 weeks after surgery. Patients were still instructed to start the trial medication as soon as possible, preferably within 2 weeks, but 8 weeks at the latest. Additionally, the definition of some outcome measurements was slightly adapted. The IRB approved all above-mentioned protocol changes. No changes were made regarding the sample size.

## Statistical analysis plan

### General principles

The randomisation code will not be broken until the last patient reaches 24 months of follow-up, all primary endpoints are reviewed by a blinded independent endpoint adjudication committee, and data cleaning is completed. The analyses will be performed after data verification and validation have been carried out and after this SAP has been accepted for publication. Analyses will be done by the investigators and biostatistician of the UPGRADE study group, using the most recent version of the SPSS statistical software at the time of analysis. All statistical tests will use a two-sided *p* value of 0.05, and two-sided 95% confidence intervals will be presented for all estimates.

### Patient flow diagram

A flow diagram of study participants will be displayed in line with the Consolidation Standard of Reporting Trials (CONSORT) recommendations and finalised upon external peer review (Fig. 1) [7].

**Fig. 1 Fig1:**
[figure not shown]
Participants flow diagram

### Treatment according to protocol and withdrawal

Treatment was regarded according to the study protocol when a patient started the trial medication within 2 weeks after surgery, but 8 weeks at the latest. A maximum mid-term break of 4 weeks was allowed during the treatment course, and good therapy compliance was defined as a minimum of 300 pills taken within a time frame of 6–8 months (> 80%). Patients were also considered as treated per protocol when the trial medication was terminated early due to reaching the primary endpoint or death. The numbers of losses to follow-up (withdrawal from follow-up) and dropouts (withdrawal from intervention) will be summarised by study arm.

### Definition of intention-to-treat, modified intention-to-treat, full analysis sets and per-protocol sets

The main analysis will follow the intention-to-treat (ITT) principle with all patients analysed in their randomisation group, irrespective of protocol adherence. Only patients with a protocol violation concerning eligibility are excluded from the ITT analysis. Protocol violation in eligibility refers to randomised patients who did not fulfil inclusion criteria or randomised patients who did meet an exclusion criterion (e.g. patients who did not undergo bariatric surgery). Patients receiving SG instead of RYGB before the approval date of the protocol amendment are also considered protocol violations in eligibility. The modified ITT analysis (mITT) will include all patients except for patients excluded from the ITT and patients without a post-randomisation measurement (e.g. patients who withdrew consent prior to administration of the trial medication or patients immediately lost to follow-up). In addition, two full analysis sets (FASs) of subjects will be made. In the first FAS, all patients will be included except for patients excluded in the mITT and patients who never commenced trial medication because of lack of motivation. Thus, patients with severe postoperative complications who were not able to start the trial medication within 8 weeks postoperatively will be included. In the second FAS, all patients will be included except for patients who were excluded in the first FAS, patients who never commenced trial medication for any reason and patients who took less than 91 pills (25% of the total amount of trial medication). We will also use two per-protocol sets (PPSs) of subjects. The first PPS will include patients who started the trial medication within 8 weeks after surgery and took a minimum of 300 pills (> 80%) within 8 months after surgery. The second PPS will include patients who started the trial medication within 2 weeks after surgery and took a minimum of 300 pills (> 80%) within 6 months after surgery. Both sets will only include patients without major protocol violations and deviations. A summary for participant inclusion and exclusion for ITT, mITT, FAS and PPS will be displayed in Fig. 2. The number of participants per data set will be displayed in supplemental Fig. 1.

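### The primary ITT set drops any randomised patient found ineligible, without requiring that the breach be identified independently of clinical course and outcome

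*SAP article*

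**What the plan says.** All of this is in the SAP article. The section defining the analysis sets opens with the principle: "The main analysis will follow the intention-to-treat (ITT) principle with all patients analysed in their randomisation group, irrespective of protocol adherence". It then makes an exception: "Only patients with a protocol violation concerning eligibility are excluded from the ITT analysis". The exception is defined broadly: "Protocol violation in eligibility refers to randomised patients who did not fulfil inclusion criteria or randomised patients who did meet an exclusion criterion". One example follows, "e.g. patients who did not undergo bariatric surgery", and one further ground is added: "Patients receiving SG instead of RYGB before the approval date of the protocol amendment are also considered protocol violations in eligibility".

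The criteria are listed under Summary study protocol. They include "existence of symptomatic gallstone disease prior to bariatric surgery", inflammatory bowel disease, other small-intestine and liver conditions that may disturb bile-salt circulation, and "hypersensitivity to ingredients of UDCA or placebo". The same section gives the order of events: "Randomisation was done prior to surgery with an online computer software program".

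The ITT set carries the primary chi-squared test (Assessment and analysis of primary outcome). Patients excluded from it are to be replaced (Patient replacement and handling of missing data).

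**The concern.** An ITT set protects the comparison because membership is settled by randomisation and not by what happens later. Removing a randomised patient is safe when the reason is objective and could not have been influenced by treatment or outcome. The two named grounds meet that test: both are settled at surgery, before the first dose, under double-blind allocation.

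The general rule does not. It reaches every criterion and is silent on how the breach comes to light. A missed history of biliary symptoms is most likely to be recognised when a patient presents with biliary symptoms again and the history is retaken. An unrecognised bowel or liver condition may surface at the same work-up. A patient with the same missed history and no event would probably never be identified. Membership of the primary set would then depend on the outcome, and each such removal takes out a primary endpoint.

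**Working it through.** **1. Is the rule confined to facts known at randomisation?** No. Randomisation preceded surgery, and the plan's own example of a violation is a patient who then had no surgery.

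**2. Would a limit to facts fixed before the first dose close the gap?** No. Symptomatic gallstone disease before surgery is by definition such a fact. The gap lies in how a breach is discovered, not in when the fact arose.

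**3. Does any planned analysis bring these patients back?**
- mITT: starts from the ITT exclusions and removes more.
- First FAS: starts from the mITT exclusions. Second FAS: starts from the first.
- Both per-protocol sets: only patients without major violations or deviations.
- Best- and worst-case scenarios: only patients lost to follow-up.

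None restores them.

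**4. Scale.** The article gives no sample size and no count of exclusions, so there is no figure to reproduce. Inputs from the article: 24-month risk of 8–15% (Abstract), used here as the placebo risk; a 50% relative reduction in the power analysis (Discussion); 1:1 allocation; two-sided 0.05. Assumed: 80% power and the share of events removed.

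Per-arm size: n = [1.960·√(2p̄(1−p̄)) + 0.842·√(p₁(1−p₁)+p₂(1−p₂))]² / (p₁−p₂)², with p₂ = p₁/2 and p̄ their mean. For p₁ = 8%, 10% and 15% this gives 553, 435 and 278.

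Suppose there is no true effect and a share f of events is removed from the UDCA arm only. The apparent risk ratio is (1−f)/(1−p·f); for p = 0.10 and f = 0.10 it is 0.90/0.99 = 0.909. Type I error of the uncorrected chi-squared test comes from 400,000 simulated trials per placebo risk; with no removal it is 0.050–0.051.

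| Placebo risk | n per arm | f | Mean removed | Apparent RR | Type I error |
|---|---|---|---|---|---|
| 8% | 553 | 5% | 2.2 | 0.954 | 0.056 |
| 8% | 553 | 10% | 4.4 | 0.907 | 0.075 |
| 8% | 553 | 20% | 8.8 | 0.813 | 0.158 |
| 10% | 435 | 5% | 2.2 | 0.955 | 0.056 |
| 10% | 435 | 10% | 4.4 | 0.909 | 0.074 |
| 10% | 435 | 20% | 8.7 | 0.816 | 0.155 |
| 15% | 278 | 5% | 2.1 | 0.957 | 0.056 |
| 15% | 278 | 10% | 4.2 | 0.914 | 0.072 |
| 15% | 278 | 20% | 8.3 | 0.825 | 0.146 |

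**5. One-sided removal with a true effect.** Assume 430 per arm and about 22 versus 43 events: RR = (22/430)/(43/430) = 0.51. Removing 3 UDCA event patients: (19/427)/(43/430) = 0.445. Removing 4 placebo event patients instead: (22/430)/(39/426) = 0.559. The shift can go either way.

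**6. Even removal.** Take 5% versus 10% and remove 10% of events in both arms. UDCA: 0.045/0.995 = 0.0452. Placebo: 0.090/0.990 = 0.0909. RR = 0.497 against 0.500. The ratio hardly moves; the cost is lost events and understated absolute risks in both arms.

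**The case against.** A reader might infer that a reaction to the trial medication could remove a patient from the primary set, because hypersensitivity is an undated exclusion criterion. The text does not support this well. The past-tense wording most naturally means status at entry. Suspected drug effects have their own route as adverse events, with skin rash listed in Table 3, and a patient who stops after a reaction stays in because adherence is disregarded. Even if such patients were dropped, losing 2–5% of event-free UDCA patients gives an apparent RR of 1.02–1.05 under no effect and a type I error of 0.051–0.056: small, and against UDCA.

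A reader might also infer that endpoints were in fact removed. Nothing in the document says so.

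The safeguards deserve credit. The trial is double-blind, and the code stays closed until follow-up, adjudication and data cleaning are complete, which prevents deliberate selection by arm. Replacement suggests that exclusions were expected during recruitment, and all included patients had undergone surgery by 22 October 2018, about two years before follow-up was due to end. Figure 2, which summarises the sets, is not shown.

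These points lower the likelihood but do not close the gap. Blinding to arm is not blinding to outcome. The adjudication committee is described as reviewing endpoints, with no stated role in eligibility. Early patients could have had events while recruitment was open, and the rule has no end date. Replacement restores numbers, not the randomised comparison.

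**Conclusion.** The point holds in a limited form and is worth correcting before the code is broken. The primary set is open to exclusions triggered by the endpoint itself, contrary to the plan's stated principle, and no planned analysis would show their effect. The number affected is likely small, and its size and direction cannot be determined from this document.

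The figures above illustrate scale only. They rest on assumed sample sizes, assumed removal shares and removal from one arm. Material bias in the risk ratio needs recognition of breaches among event patients to differ between arms, by mechanism or by chance; if it is even, the ratio is almost unchanged. The two named grounds, no bariatric surgery and SG before the amendment, are not part of the problem.

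**What to change.** Four changes:

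- Limit exclusions from the primary set to the two named grounds settled before the first dose: no bariatric surgery, and SG before the approval date of the amendment.
- Keep all other eligibility violators in the ITT set, and exclude them only from the per-protocol sets. The Discussion already handles patients who received the other type of surgery in this way.
- Have the exclusion list fixed before code break by people who see neither allocation nor outcome.
- Add a sensitivity analysis of the primary outcome restoring all randomised patients with outcome data, and report exclusions by arm and reason, including those with no outcome data.

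The cost is a few sentences in the SAP, one extra run, and slight dilution from a few ineligible patients kept in.

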**Fig. 2 Fig2:**
[figure not shown]
Summary of participant inclusion and exclusion for ITT, mITT, FAS and PPS

### Patient replacement and handling of missing data

Patients not fulfilling eligibility criteria resulting in the exclusion of the ITT analysis will be replaced. If outcome data cannot be obtained by a study follow-up visit at the outpatient clinic, the patient will be contacted by telephone to gather primary and most secondary outcome data. The postoperative ultrasound of these patients and all data on patients that cannot be contacted will be considered missing. For missing data, a multiple (% of missing data) imputation approach will be selected and justified at the time of analysis, based on the observed missing data pattern and using relevant patient characteristics and outcome predictors. The imputed values will be primarily estimated within the observed data ranges. We will not impute missing values if the percentage missing is below 2. If the missing data appear not missing at random, a worse- and best-case scenario will be run, in which all patients lost to follow-up in the placebo arm are considered free of symptomatic gallstone disease, and all patients lost to follow-up in the UDCA arm are considered not free of symptomatic gallstone disease, and vice versa. Missing values of baseline characteristics will not be imputed. Mixed effects modelling will be applied for the analysis of repeated measures from questionnaire data, thereby simultaneously accounting for missing data.

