### Assessment and analysis of primary outcome

The primary outcome is the proportion of patients with symptomatic gallstone disease within 24 months of follow-up. Symptomatic gallstone disease is defined as a biliary disease (biliary pancreatitis, acute cholecystitis, choledocholithiasis, cholangitis or biliary colics) for which a hospital visit or admission was required. To assess the primary outcome, follow-up appointments are held at 6 and 16 weeks, and 6, 12 and 24 months by one of the blinded investigators. All primary endpoints will be reviewed by a blinded independent endpoint adjudication committee.

To provide an estimator of the effectiveness of UDCA, we will perform a standard ITT analysis. The difference between outcomes by study arm will be compared using the chi-squared test with a risk ratio (unless editors of the accepting journal suggest to report odds ratio) as an indicator for effect size, as shown in Table 2. The results of the mITT and other data sets will be provided in a supplementary appendix, if no contradictory findings are to be reported.

**Table 2 Tab2:** Gallstone-related outcomes

	UDCA (***n***=)	Placebo (***n***=)	Effect size	***p***
*Primary outcome*				
**Symptomatic gallstone disease**—*n* (% *n*/*N*)				
Biliary pancreatitis				
Acute cholecystitis				
Choledocholithiasis				
Cholangitis				
Biliary colic				
*Secondary outcomes*				
**Presence of gallstones/sludge on ultrasound at 24 months**—*n* (% *n*/*N*)				
**Newly formed gallstones/sludge on ultrasound at 24 months**—*n* (% *n*/*N*)				
**Cholecystectomy**—*n* (% *n*/*N*)				

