We are aware that many studies have reported poor compliance of UDCA after bariatric surgery. Consequently, there is a chance that the expected attrition rate will be exceeded. If this is the case, we assume that we will not need a higher number of patients to assure the availability of sufficient evaluable patients, because the relative reduction is probably larger than the 50% reduction used in the power analysis.

In our trial, the postoperative ultrasound is performed during a regular follow-up visit at the outpatient clinic. Due to the unforeseen and unique bankruptcy of two participating centres, and the coronavirus disease (COVID-19) pandemic, the regular follow-up schedule was suspended temporarily. Therefore, we decided to maintain a relatively large window (18 to 30 months) in which the postoperative ultrasound—originally scheduled at 24 months—has to be carried out. We will explore whether the contrast between the two study arms is stable across different time frames in order to assess the impact of the logistic artefact.

The results of the UPGRADE trial will optimise the postoperative management of bariatric patients and probably lead to a reduction of patients with symptomatic gallstone disease. This trial has the potential to affect daily clinical practice and improve patient outcomes. Second, cost-effectiveness, cost-utility and budget impact analyses of postoperative UDCA prophylaxis may demonstrate the societal value of prophylactic UDCA treatment for health care providers, insurers and taxpayers.

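### The SAP appears to set the number of imputations equal to the percentage missing, which leaves enough simulation noise for a primary p value close to 0.05 to change sides with the random seed

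*SAP article*

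**What the plan says.** The section on patient replacement and handling of missing data states: "For missing data, a multiple (% of missing data) imputation approach will be selected". The same sentence leaves the choice and its justification until the analysis is done. The section adds a lower limit: "We will not impute missing values if the percentage missing is below 2". It gives no explicit number of imputations, no minimum, no seed and no expected percentage missing.

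The imputed values bear on the main result. The ITT set keeps every eligible randomised patient, and patients who cannot be contacted count as missing. For the primary outcome, "The difference between outcomes by study arm will be compared using the chi-squared test with a risk ratio". Under General principles, "All statistical tests will use a two-sided *p* value of 0.05".

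**The concern.** A percentage placed inside the phrase for multiple imputation reads most naturally as a rule for m: 2% missing gives 2 imputations, 5% gives 5, 20% gives 20. Such a rule keeps the loss of efficiency small. It does not make the p value repeatable, because a different seed gives a different pooled estimate and standard error.

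The result is judged against a fixed threshold. If the p value lies close to it, two analysts who apply this rule to the same data with different seeds could report opposite conclusions on the primary outcome. The seed is then an unrecorded analysis choice. That sits badly with the Discussion, which gives reproducibility as a reason for publishing the plan.

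**Working it through.** The SAP gives no number of imputations, sample size, power or expected missingness, so there is no figure of its own to reproduce.

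**Inputs from the SAP.** Two-sided 0.05 threshold; 1:1 allocation; no imputation below 2% missing; a background event rate of 8–15% within 2 years (Introduction); a 50% relative reduction in the power analysis (Discussion).

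**Assumptions.** m equals the percentage missing, so m = 100f for missing fraction f. Outcomes are missing at random within arm. The fraction of missing information (FMI) is about f. For the simulation, 430 or 500 patients per arm. For scale, 80% power for a 50% reduction needs 553, 435 and 278 per arm at placebo rates of 8%, 10% and 15%.

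**Step 1: noise between seeds.** SD(z) ≈ √(FMI/m) = √(f/100f) = √0.01 = 0.10 at every f. Near p = 0.05, SD(p) ≈ 2φ(1.96) × 0.10 = 2 × 0.0584 × 0.10 ≈ 0.012.

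**Step 2: chance of landing on the other side of 0.05.** This is Φ(−|z − 1.96|/0.10), where the true p is the value with unlimited imputations.

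| True p | z | Distance from 1.96 | In SDs | Chance |
|---|---|---|---|---|
| 0.03 | 2.170 | 0.210 | 2.10 | 1.8% |
| 0.04 | 2.054 | 0.094 | 0.94 | 17% |
| 0.045 | 2.005 | 0.045 | 0.45 | 33% |
| 0.055 | 1.919 | 0.041 | 0.41 | 34% |
| 0.06 | 1.881 | 0.079 | 0.79 | 21% |
| 0.07 | 1.812 | 0.148 | 1.48 | 7% |

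**Step 3: simulation.** Fixed data sets were re-imputed with 4,000 seeds per setting. Outcomes were imputed within arm with posterior draws. The log risk ratio was pooled by Rubin's rules, with a Wald test in place of a pooled chi-squared.

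| Missing, m | Per arm, placebo rate | True p | 95% range over seeds | Changed sides |
|---|---|---|---|---|
| 2%, 2 | 430, 10% | 0.045 | 0.029–0.082 | 40% |
| 5%, 5 | 430, 10% | 0.043 | 0.026–0.073 | 29% |
| 10%, 10 | 430, 10% | 0.037 | 0.022–0.065 | 15% |
| 20%, 20 | 500, 8% | 0.044 | 0.026–0.077 | 37% |

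The simulated FMI matched the missing fraction. The instability at 20 imputations is like that at 2, as step 1 predicts.

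**Step 4: chance over all results.** The probability that one run departs from the unlimited-m verdict is about the density of z at 1.96 times the mean absolute noise, 0.10 × √(2/π) = 0.080. With 80% power, z is about N(2.8, 1), so the density is φ(0.84) = 0.280 and the chance is 0.280 × 0.080 ≈ 2.2%. At 90% power it is about 1.4%, and under the null about 0.9%.

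**Step 5: a fixed m, true p of 0.045.**
- m = 100: SD(z) = √(0.10/100) = 0.032 at 10% missing and 0.045 at 20%; chance 7.9% and 15.9%.
- m = 500: SD(z) = 0.014 and 0.020; chance about 0.1% and 1.3%.

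**The case against.** Several points on the other side stand.

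- The SAP never says outright that m equals the percentage missing, and it leaves the approach to the time of analysis. If the parenthesis means something else, the article fixes no number. The same edit settles that too.
- Good predictors could bring the FMI below the missing fraction, and the SAP intends to use outcome predictors. If the percentage is taken over the whole data set, missing ultrasounds could raise m. Either would reduce the noise. Telephone contact may also keep the primary outcome under 2% missing, where nothing is imputed and the issue disappears.
- A condensed article may leave the seed to the full plan or the code. That is fair for the seed alone, but the point here is the rule that the article prints.
- Confidence intervals are to be reported with all estimates, so the reader does not depend on the threshold alone.

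A reader might infer more than the documents support:

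- **That the trial will use between 2 and 10 imputations.** Only the lower end follows from the SAP, and only on the reading above. No expected missingness is given, so no upper end can be named.
- **That a small m is itself the cause.** It is not: 20 imputations at 20% missing are as noisy as 2 at 2%. The cause is the proportional rule.
- **That the primary conclusion is broadly at the mercy of the seed.** Only borderline results are affected. Nor is it evidence that about half of runs fall on each side when the true p is exactly 0.05, since that happens at any m.

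**Conclusion.** The concern holds in a limited form. On the likeliest reading, the printed rule gives an SD between seeds of about 0.10 in z and 0.012 in p near 0.05, at any percentage missing from 2% upwards. A primary p between about 0.03 and 0.07 could change sides. Outside that band the risk is very small, and averaged over possible results it is about 2%.

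These figures rest on m equal to the percentage missing, on FMI about equal to the missing fraction, on outcomes missing at random within arm and, for the overall chance, on 80% power, which the SAP does not state. The analysis is not invalid. But a clearly better rule is available at almost no cost, so the SAP should change it.

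**What to change.** Replace the parenthesis by a fixed number of imputations for the primary outcome that does not depend on the percentage missing. At least 100 would be a clear improvement; 500 makes a change of sides rare even at a true p of 0.045. The exact number is a matter of the tolerance that the sponsor accepts. Record the number and the random seed before the randomisation code is broken.

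The cost is one phrase in the SAP and a little computing time. Design, hypothesis and data collection are untouched.
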